#### Exclusion criteria

This study will exclude [1] patients who were scheduled for bilateral breast surgery; [2] immediate breast reconstruction surgery; [5] mental impairment leading to inability to cooperate; [6] current pregnancy or plans to become pregnant within the 1 year; and [7] any other condition or intercurrent illness (as assessed by the investigator).

#### Ethics and informed consent

The study protocol was approved by the Medical Ethics Committee of Severance Hospital, Yonsei University Health System, Seoul, Korea (4-2022-0027). This study will be conducted in accordance with the principles of the Declaration of Helsinki and Good Clinical Practice guidelines, including data and patient privacy protection. All the participants will provide written informed consent.

#### Sample size

The calculation for sample size was based on a previous study that evaluated the effects of 16 week mixed strength and endurance exercise on insulin levels in patients with breast cancer [31]. Based on a power of 80%, two-sided statistical significance level of 5%, and medium-sized effect size, the minimum required sample size would be 80 participants. Considering the dropout rate to be 20%, 96 patients with breast cancer are needed for the current study.

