**Methods:**

This 12-month RCT includes 96 patients with (stages 1–3) breast cancer randomly assigned to the exercise or control groups. Participants in the exercise group will receive an exercise program tailored to their phase of treatment, type of surgery, and physical function. During post-operative recovery, exercise interventions will be emphasized to improve shoulder range of motion (ROM) and strength. During chemoradiation therapy, exercise intervention will focus on improving physical function and preventing loss of muscle mass. Once chemoradiation therapy is completed, exercise intervention will focus on improving cardiopulmonary fitness and insulin resistance. All interventions will be home-based exercise programs supplemented with once-monthly exercise education and counseling sessions. The main outcome of the study is fasting insulin level at baseline, 6 months, and 1 year post-intervention. Our secondary outcomes include shoulder ROM and strength at 1 month and 3 months, body composition, inflammatory markers, microbiome, QoL, and physical activity levels at 1 month, 6 months, and 1 year post-intervention.

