## Randomization

Eligible participants will be randomly assigned to the exercise or control group, considering age, surgery method, and neoadjuvant chemotherapy as potential confounders. Each group would be matched into pairs such that the average age, surgical method, and neoadjuvant chemotherapy percentage are approximately equal (1:1 ratio). The exercise group will be provided with a systematic exercise program from post-operative day (POD) 1 to 12 months after surgery. The control group will receive the same preoperative and post-operative medical care and treatment as the exercise group (i.e., the usual care group thereafter), except for post-operative exercise. To evaluate the effects of the exercise intervention, measurements will be conducted five times for all the participants. The registration number of the Korean Clinical Trials Registry is KCT0007853. Data will be de-identified for analysis, and only study leaders at the university hospital will have access to identifiable information for all participants.

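### The 20% dropout allowance is miscalculated: 96 enrolled leaves about 77 evaluable participants, below the plan's own minimum of 80

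*Protocol article*

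**What the plan says.** The Sample size section of the protocol article gives the design inputs as follows: "Based on a power of 80%, two-sided statistical significance level of 5%, and medium-sized effect size". From these it concludes that "the minimum required sample size would be 80 participants". The dropout step comes next: "Considering the dropout rate to be 20%, 96 patients with breast cancer are needed for the current study".

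The Methods part of the Abstract repeats the total as the number randomised: "This 12-month RCT includes 96 patients with (stages 1–3) breast cancer randomly assigned to the exercise or control groups". The Randomization section gives a 1:1 allocation, so 80 means 40 per arm and 96 means 48 per arm.

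The article nowhere defines dropout in an unusual way, and it gives no other basis for 96.

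**The concern.** The allowance for dropout has one purpose: that the minimum number is still there for analysis after the expected losses. Here the three stated numbers (80 needed, 20% lost, 96 enrolled) do not fit together. The 96 looks like the result of multiplying by 1.20 where the plan should have divided by 0.80.

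A reader will take the section to mean that the trial keeps 80% power if one in five participants is lost. If the inflation is wrong, that assurance is wrong too. The primary outcome is fasting insulin at 12 months, so someone who leaves before then has no primary measurement.

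**Working it through.** **Inputs**

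- Minimum required number: 80 (Sample size).
- Dropout rate: 20% (Sample size).
- Planned enrolment: 96 (Sample size; Abstract, Methods).
- Power 80%, two-sided 5%, effect described only as medium (Sample size).
- Allocation 1:1 (Randomization).

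**Reproducing the plan's figure**

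n × (1 + dropout) = 80 × 1.20 = 96. This matches exactly. It allows for 16 losses, and 16 / 80 = 20%. The 20% has thus been taken of the completers.

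**Inflation for a rate among those enrolled**

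n / (1 − dropout) = 80 / 0.80 = 100, or 50 per arm. Check: 100 × 0.80 = 80.

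**What 96 delivers**

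- Evaluable at 20% dropout: 96 × 0.80 = 76.8, or 38.4 per arm. In whole people this is 77 in total, or 76 if rounded down to equal arms of 38.
- Shortfall in evaluable participants: 80 − 76.8 = 3.2, so 3 to 4 people. Shortfall in enrolment: 100 − 96 = 4.
- Largest dropout at which 96 still leaves 80: 1 − 80/96 = 16/96 = 16.7%.

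**Effect on power (conditional)**

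The article gives no numeric effect size and names no test for the calculation. To size the loss, assume a two-sided 5% two-sample t-test for which 40 per arm gives exactly 80% power. Solving the noncentral t distribution for the effect gives d = 0.634.

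| Evaluable | Power at d = 0.634 | Effect detectable with 80% power |
|---|---|---|
| 80 (40 per arm) | 80.0% | 0.634 SD |
| 76.8 (38.4 per arm) | 78.3% | not computed |
| 76 (38 per arm) | 77.9% | 0.651 SD |

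If medium is instead read as d = 0.5, also an assumption, the same test has 59.8% power at 80 evaluable, 58.0% at 76.8 and 57.6% at 76. The absolute level depends heavily on the effect assumed, but the loss caused by the dropout error is about 2 percentage points either way.

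**The case against.** The strongest objection is that the error is immaterial. About three people out of 80 are at issue, power moves by roughly two points, and 96 still protects 80 completers up to 16.7% dropout. The 20% is itself a planning guess, and no feature of the design or analysis turns on the difference. All of this is fair, and it limits the weight of the point. It does not make the sentence correct: the article calls 80 a minimum and states no margin above it.

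A second objection is that the power figures rest on a back-solved effect and an assumed test, while the Statistical analysis methods section plans two-way repeated-measures ANOVA for fasting insulin along with t-tests at each time point. This also stands. The 77.9% and 78.3% are illustrations under a stated assumption. The head count, 76.8 against 80, needs no such assumption.

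Two further defences fail. Multiplying by 1.20 would be right only if dropout were counted per completer, and the article does not say so. Nor can a fuller protocol or SAP cure the problem, because nothing is missing here: the three published numbers disagree with each other.

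Whether 80 is itself well founded is a separate question. A two-sample t-test at d = 0.5 would need about 128 in total. That neither causes nor removes the dropout error.

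**Conclusion.** The concern holds. Under the plan's own dropout rate, 96 enrolled leaves 76.8 evaluable, short of the stated minimum by about 3 people, or by 4 if rounded down to equal arms. This rests only on the article's 80, 20% and 96, and on reading a dropout rate in the ordinary way as a share of those enrolled. It is true for any effect size.

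The cost in power is about 2 points (80% to about 78%), or a rise in the detectable effect from 0.634 to 0.651 SD. Those figures assume a two-sample t-test in which 80 gives exactly 80% power. The sentence should be corrected, but the error does not threaten the trial.

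**What to change.** Rewrite the dropout sentence in one of three ways.

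1. Keep 96 and 20%: say that 96 enrolled with 20% dropout leaves about 76 evaluable participants (38 per arm), and quote the power or detectable effect for that number, naming the test and the numeric effect size used.
2. Keep 96 and 80: say that 96 allows for dropout of up to 16.7%. This should be chosen only if that rate is a credible expectation, since the article offers no support for it.
3. Keep 80 and 20%: raise enrolment to 100 (50 per arm), and change the figure in both the Sample size section and the Abstract.

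The first is the most direct. Options 1 and 2 cost one sentence and leave recruitment and conduct unchanged; option 1 makes the stated power slightly less favourable. Option 3 costs four more participants.

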### Recruitment

The current study will recruit participants for 12 months on a roll-in basis. Eligible participants will be recruited by physicians and specialists. Physicians will be informed about the study and exercise specialists will provide a study flyer that includes contact details and related information. Exercise specialists will obtain written consent from participants who meet the inclusion criteria. Eligible participants will undergo baseline medical examinations and physical performance tests. They will immediately receive appointments and necessary information about the study. Further details are presented in the study flowchart (Fig. 1).

**Fig. 1 Fig1:**
[figure not shown]
Overview of the protocol study

## Randomization

Eligible participants will be randomly assigned to the exercise or control group, considering age, surgery method, and neoadjuvant chemotherapy as potential confounders. Each group would be matched into pairs such that the average age, surgical method, and neoadjuvant chemotherapy percentage are approximately equal (1:1 ratio). The exercise group will be provided with a systematic exercise program from post-operative day (POD) 1 to 12 months after surgery. The control group will receive the same preoperative and post-operative medical care and treatment as the exercise group (i.e., the usual care group thereafter), except for post-operative exercise. To evaluate the effects of the exercise intervention, measurements will be conducted five times for all the participants. The registration number of the Korean Clinical Trials Registry is KCT0007853. Data will be de-identified for analysis, and only study leaders at the university hospital will have access to identifiable information for all participants.

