### Eligibility criteria

#### Inclusion criteria

Eligibility criteria will include the following: [1] women aged 19–70 years; [2] patients with histologically confirmed stage I, II, and III breast cancer; [3] medically suitable for evaluation and participation in exercise intervention; [4] no evidence of distant metastasis or locally recurrent breast cancer; and [5] ability to understand and provide written informed consent in the Korean language.

**Table 1 Tab1:** Flow diagram for the schedule of enrollment, interventions, and assessments

TIME POINT	VISIT 1	VISIT 2 *[Phase 1]*	VISIT 3 *[Phase 1]*	VISIT 4 *[Phase 2]*	VISIT 5 *[Phase 3]*
	Baseline, (Before surgery)	POD 1	1 month from the baseline (± 2 weeks)	6 months from the baseline (± 1 month)	12 months from the baseline (± 1 month)

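### The stated pair matching to equal group averages conflicts with random assignment; taken literally under rolling entry it would fix up to half of the assignments, and the stated insulin analyses ignore the balancing factors.

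*Protocol article*

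**What the plan says.** The Randomization section makes two statements in succession. Participants will be "randomly assigned to the exercise or control group, considering age, surgery method, and neoadjuvant chemotherapy as potential confounders". Then: "Each group would be matched into pairs such that the average age, surgical method, and neoadjuvant chemotherapy percentage are approximately equal (1:1 ratio".

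The schedule around the allocation is as follows.
- Recruitment: "The current study will recruit participants for 12 months on a roll-in basis".
- Table 1 heads Visit 1 "Baseline, (Before surgery".
- Randomization: the exercise group "will be provided with a systematic exercise program from post-operative day (POD) 1".

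On staff, the Recruitment section says: "Exercise specialists will obtain written consent from participants who meet the inclusion criteria". The Phase 1 to Phase 3 exercise descriptions also have exercise specialists recommending how each exercise is performed. The comparison arm carries on with its routine activities, so the arms are visible to staff and patients.

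For fasting insulin, the Statistical analysis methods section plans a two-way repeated-measures ANOVA, and independent t-tests between groups at each time point. ANCOVA is planned for body composition, physical activity and complications, adjusted for baseline value and surgical method. No stated analysis uses the pairs, age or neoadjuvant chemotherapy.

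**The concern.** The second sentence on allocation does not describe a random mechanism. The averages of two groups exist only once the groups exist, so making them similar is a result to aim at, not a way of drawing an assignment.

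Matched-pair randomisation is sound when both members are known before a single draw decides who goes where. With rolling entry and a start on the day after surgery, that will seldom be possible. If pairs are completed as patients arrive, the first member is randomised and the second takes what is left.

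Anyone who knows the earlier assignments and the matching factors could then foresee the second member's arm before consent. Enrolment could be hastened, deferred or discouraged accordingly. In an unblinded exercise trial this could let more motivated or fitter patients collect in one arm, and fasting insulin could differ for that reason.

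A second, smaller matter is precision. If allocation is balanced on prognostic factors that the analysis ignores, the reported standard errors do not reflect the balance achieved.

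**Working it through.** The article states no block size, strata or allocation probability, so it has no figure of its own to reproduce. The steps below follow the literal rule.

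**1. Can a partner be known in time?** Inputs: 96 patients (Sample size), 12 months of recruitment (Recruitment), baseline before surgery (Table 1), exercise from the first post-operative day (Randomization).
- Entry rate: 96 / 12 = 8 patients per month.
- Assumption: the three factors form 8 to 18 equally likely cells (2×2×2 = 8; 3×2×2 = 12; 3×3×2 = 18 for age bands × surgery types × neoadjuvant yes/no).
- Entrants per cell: from 8/8 = 1 per month down to 8/18 = 0.44 per month, so the mean gap between two patients of the same type is about 1 to 2.25 months.
- Time available: from the pre-surgery baseline to the day after surgery. The Exploratory objective counts changes from the day before surgery.

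The first member of a pair would therefore usually have to be allocated before the second is known.

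**2. Ceiling.** If every patient finds a partner, 96 / 2 = 48 assignments (50%) are fixed by the earlier one.

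**3. Allowing for patients left without a partner.** A cell with an odd count leaves one patient over, and about half of the cells will be odd.
- 8 cells: about 4 left over; (96 − 4)/2 = 46; 46/96 = 47.9%.
- 12 cells: about 6 left over; (96 − 6)/2 = 45; 45/96 = 46.9%.
- 18 cells: about 9 left over; (96 − 9)/2 = 43.5; 43.5/96 = 45.3%.

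A simulation of 96 sequential entrants (500 runs per setting) gave the same shares: 47.9%, 46.9% and 45.3%.

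**4. How often could the next arm be guessed?** With determined share D, and full knowledge of past assignments and covariates, the correct-guess rate is D + (1 − D) × 0.5.
- 8 cells: 0.479 + 0.521 × 0.5 = 0.740.
- 18 cells: 0.453 + 0.547 × 0.5 = 0.727.

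Under simple randomisation it is 0.50.

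**5. Alternatives in the same simulation** (ranges over the three cell structures; imbalance is the largest between-arm difference within a factor, averaged over factors and runs):

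| Method | Certain in advance | Guessable with full knowledge | Imbalance (patients) |
|---|---|---|---|
| Simple randomisation | 0% | 50% | 7.6–8.1 |
| Literal sequential pairing | 45–48% | 73–74% | 1.4–2.2 |
| Minimisation, no random element | 76–77% | 88–89% | 0.7–1.0 |
| Minimisation, probability 0.8 | 0% | 74% | 1.6–1.9 |
| Minimisation, probability 0.7 | 0% | 66% | 2.4–3.0 |

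Minimisation with probability 0.8 gives about the same balance as pairing with no assignment certain, although the average guess rate is similar. Lowering the probability to 0.7 reduces guessing and gives up a little balance. Stratified blocks were not simulated.

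**6. Analysis.** Let R² be the share of outcome variance explained by the balanced factors. With n per arm, the variance of the difference in means is roughly (1 − R²) × 2σ²/n, while an unadjusted test uses 2σ²/n. The standard error is then too large by a factor of about 1/√(1 − R²). The article gives nothing from which to set R², so only the direction is claimed.

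**The case against.** The strongest reply is that the sentence is an awkward statement of an aim. It follows a statement that assignment is random, and averages and percentages describe groups rather than pairs. The authors may mean stratification or minimisation, in which case no assignment need be certain. A journal article may also leave sequence generation and concealment to the full protocol, and its flowchart is not shown. This stands in part: silence on who holds the sequence is not a fault. It does not rescue the sentence, which names pair matching and does not describe any of those methods.

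Several stronger readings are tempting, and the documents do not support them.
- **That concealment is broken.** Nothing says that enrolling staff see earlier assignments and covariates. Their double role makes foresight possible but does not establish it.
- **That staff choose the arm to even out the averages, so that all assignments could be steered.** No such procedure is described.
- **That balance is impossible under rolling entry.** Minimisation with a random element achieves it approximately.
- **That 48 is a minimum.** Under sequential pairing it is the ceiling, because some patients remain unpaired.
- **That the bias can be put in figures.** The article calls its effect size only medium and gives no basis for the size of any selection effect.

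On the analysis, standard errors that are too large cost power and do not create false positives. Surgical method is already in the ANCOVA for the other outcomes, and further adjustment may be set out in a statistical analysis plan that is not shown. That limits the weight of the analysis point, but the analyses stated for fasting insulin still do not use the factors.

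**Conclusion.** The concern holds as a defect in a stated rule. Pair matching towards equal averages conflicts with the random assignment stated just before it. Applied literally to patients who enter singly and start on the day after surgery, it would fix up to 48 of 96 assignments, or about 45–48% once unpaired patients are allowed for.

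That range assumes 8 to 18 equally likely covariate cells, exact matching within a cell, and the opposite arm for the second member; the article specifies none of these. The consequence is a risk to concealment, made more plausible by visible arms and by exercise specialists who both take consent and guide the exercises. It is not evidence that concealment has failed.

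The loss of precision from leaving the balancing factors out of the fasting insulin analyses is secondary. Its direction is clear only where those factors are prognostic, and its size cannot be worked out from the article.

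**What to change.** 1. Replace the pair-matching sentence with a named, concealed random method. Two suitable examples are a computer-generated list stratified by surgical method and neoadjuvant chemotherapy with randomly varying block sizes, and central minimisation on age, surgical method and neoadjuvant chemotherapy with a random element.
2. State that each assignment is released only after consent and the baseline tests are complete.
3. Adjust the fasting insulin analysis for baseline insulin, age, surgical method and neoadjuvant chemotherapy.

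If the full protocol already specifies such a method, only the article's wording has to be brought into line with it.

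The cost is a change of wording, a generated list or a central randomisation service, and three balancing covariates plus baseline insulin in the primary model. The one drawback is that balance on age becomes approximate; with minimisation at probability 0.8, the simulated imbalance on the three factors was under 2 patients on average.

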### Intervention

#### Usual care group

Participants in the usual care group will be instructed to continue their routine activities. Twelve months after surgery, the usual care group will receive exercise counseling, exercise education, and an exercise diary, based on the measurement results.

#### Exercise group

The exercise group will receive the usual care and exercise programs based on previously used exercise programs in clinical trials (KCT0006997). The exercise program according to the phases of cancer trajectory will consist of supervised and home-based exercises. Up to 1 month after surgery, weekly supervised exercises and daily home-based exercises will be provided. Thereafter, supervised exercise will be provided once per month, along with home-based exercise. The purpose of the supervised exercise session was to educate participants, enabling them to perform exercise daily at home with the help of exercise videos that included detailed instructions on how to perform each exercise. The exercise programs will be tailored based on the patient’s condition and each time point after surgery [1 month from the baseline (± 2 weeks); Phase 1, 6 months from the baseline (± 1 month); Phase 2, 12 months from baseline (± 1 month); Phase 3] (Fig. 2).

**Fig. 2 Fig2:**
[figure not shown]
Overview of the Three Phases

#### Exercise program

Figure 2. Overview of three phases.

The exercise program was developed (Steps 1 to 9) based on a review of the literature [32, 33], an established understanding of patient characteristics [28, 34], expert panel meetings, feasibility studies,

and revision of the exercise program [35, 36]. The exercise program was divided into three phases according to the individual treatment period: surgery, chemoradiation therapy, hormone therapy, and the patient’s condition (Fig. 2). The exercise program consists of seven different intensities, standards for the application of exercise programs (Supplementary 1,2,3,4,5,6,7), and an exercise diary. Post-operative breast cancer patients and medical staff reviewed the safety of the exercises and the feasibility of the exercise evaluation design through a feasibility study [35]. The program included stretching and resistance exercise components for recovery of shoulder ROM, recovery of shoulder strength, reduced pain and discomfort after breast cancer surgery, and stretching of tight muscles (e.g., pectoralis major and minor muscles), and resistance exercises for muscle weakness (e.g., trapezius and rhomboid major and minor muscles).

